### Statistical analyses

First, to investigate potential differences between the two groups at baseline, we will use parametric and nonparametric descriptive statistics, as appropriate. For the main analyses concentrating on primary and secondary outcomes, linear growth curve models for normally distributed outcome measurements will be used, logistic regression for binary data, and Poisson regression models for ordinal data. Results will be expressed in terms of comparison of the slopes for interval data, odds ratios for binary data and incidence rate ratios for ordinal data. Furthermore, we will perform explorative analyses regarding mechanisms of change using both variable and person-centered approaches. All analyses will be conducted according to intention-to-treat principles.

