### Procedure

All patients referred to one of the mental health care institutes were invited to attend an intake appointment. Patients who were deemed eligible received more information about the study and, if they were interested, a new appointment was set during which the BPSDI [39], and SCID-II [38] interviews were administered and other eligibility criteria were assessed. If patients met inclusion criteria, they provided informed consent and were randomized to either MBT or TAU by an independent researcher using a computerized 1:1 algorithm. Patients were subsequently asked to complete the baseline measures (see Figure 1). It was preferred that patients completed the measures in the clinic; however if patients insisted, they were allowed to complete questionnaires at home, in which case patients were asked to return the questionnaires within a week by regular mail.

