### Treatments

#### Day hospital MBT

MBT-DH is an intensive, manualized specialist treatment for patients with BPD that has been described in detail elsewhere [23,35]. Briefly, MBT-DH in this study consists of an intensive day-hospitalization programme of 18 months followed by a maximum of 18 months of maintenance mentalizing (group) therapy. The day-hospital program, covering five days per week and 4.5 hours per day, includes the following components: (a) implicit mentalizing groups (i.e., daily group psychotherapy and weekly individual psychotherapy, and individual crisis planning from a mentalizing perspective) and (b) explicit mentalizing groups (i.e., art therapy twice a week, mentalizing cognitive group therapy, and writing therapy). The week’s program is ended by a social hour and a community meeting. Patients can also consult a psychiatrist once a week and medication is offered following American Psychiatric Association guidelines.

The treatment goals of MBT-DH are: (a) to engage the patient in treatment; (b) to reduce psychiatric symptoms, particularly self-harm and parasuicidal behaviour; (c) to improve social and interpersonal functioning; and (d) to foster more appropriate health care usage and prevent hospital admissions and prolonged inpatient care. To achieve these goals, components of the programme focus on enhancing the capacity for mentalizing.

As outlined above, the assumption is that by enhancing their mentalizing capacity, particularly in high arousal contexts, patients will show improvements in understanding themselves and others, leading to a decreased need to rely on maladaptive coping strategies to deal with feelings of inner emptiness and “badness”, impulsivity and relationship conflicts.

The MBT teams consist of a total of three certified and registered psychologists, two psychotherapists, one psychiatrist, four sociotherapists, and a creative therapist. All clinicians who are involved in providing MBT-DH followed an MBT training programme led by a certified MBT trainer in The Netherlands, who also acted as a consultant before and during the study and provided supervision in the initial stages of the trial.

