### Sample size and power calculation

Based on records of 2008, we estimated the number of new referrals per year to Arkin and De Viersprong. On average, the total annual number of new referrals was 265 at De Viersprong and 230 at Arkin. Out of all newly referred patients, 154 suffered from a severe BPD and met the inclusion criteria for this study. Assuming a refusal rate of 35%, this means that on average 8.1 patients could be included each month. Therefore, we expected to be able to recruit and assess 108 patients (54 in each arm) during a recruitment window of 14 months. Figure 1 shows the expected flow of participants from recruitment through the beginning of the study.

In this study the primary clinical outcome variable is the total score on the BPDSI, an index of the severity of BPD manifestations. Bales and colleagues [35] found a large effect size of 1.23 on the BPDSI after 18 months of MBT-DH, in a sample of 45 BPD patients. Although Bateman and Fonagy [33] used another index for the severity of borderline symptoms (the Zanarini Rating Scale for Borderline Personality Disorder, a clinician-administered scale for the assessment of change in DSM-IV borderline psychopathology [87]), they also found a large effect size 5 years after MBT (a difference of 64% between TAU [mean = 15.1, SD = 5.3) and MBT-DH [mean = 5.5, SD = 5.2; effect size = 1.8]). Although within-group effect sizes for MBT can be expected to be large, the specialist TAU investigated in the present study may be more effective than TAU provided in the UK. Yet, given differences in effect sizes in previous trials, particularly in the long term, we expect MBT-DH patients to improve at least 20% more than TAU patients on the BPDSI at 18 months after the start of the intervention. With a sample of 54 patients per group, an effect size of at least .65 on the BPDSI could be detected with a power of 92% (α = .05, *β =* .083), which reflects a reasonable, realistic and clinically relevant effect.

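### The slope comparison named for continuous outcomes is tied to neither the 18-month effect behind the sample size nor the 36-month hypothesis, and can misstate the 18-month effect if change is not linear

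*Protocol article*

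**What the plan says.** In the Statistical analyses section, "linear growth curve models for normally distributed outcome measurements will be used" for the main analyses of primary and secondary outcomes, and "Results will be expressed in terms of comparison of the slopes for interval data". The section mentions no knot, no non-linear time term and no contrast at a named month.

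The Sample size and power calculation section states the expectation for one time point: "we expect MBT-DH patients to improve at least 20% more than TAU patients on the BPDSI at 18 months after the start of the intervention". For 54 patients in each arm it then claims that "an effect size of at least .65 on the BPDSI could be detected with a power of 92" per cent.

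The Research aims and hypotheses section and the Discussion expect MBT-DH to do better especially at 36 months.

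The MBT-DH arm receives "an intensive day-hospitalization programme of 18 months followed by a maximum of 18 months of maintenance" therapy, whereas the Treatment as usual section sets no time limit and describes no planned change at month 18.

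The Procedure section schedules assessments at baseline and every 6 months to month 36. It names the BPDSI explicitly only at eligibility screening and at month 36.

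**The concern.** The article works with three quantities: a powered difference at 18 months, a hypothesised difference at 36 months, and a reported difference in slopes. They say the same thing only if the gap between the arms grows in a straight line. The design gives a reason to doubt that, because treatment intensity changes at month 18 in one arm only. The article's own background describes two other patterns: in the first MBT-DH trial an early advantage was maintained during follow-up, and in an outpatient MBT trial an advantage appeared only at long-term follow-up.

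At stake is whether the main result answers the question for which 108 patients were justified. A slope difference could be reported and read as an 18-month effect when it is not one. It also could not tell an early, maintained gain from a late one.

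**Working it through.** **Inputs from the protocol article.** 54 patients per arm, allocated 1:1; effect size 0.65; α = .05; power 92%, β = .083; visits at t = 0, 6, 12, 18, 24, 30 and 36 months.

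**Assumptions, because the article gives no figures.** BPDSI is measured at all seven visits; data are complete; the SD is 1 (for random slopes, at baseline); there is one straight line per arm with a free intercept; the arms are equal at baseline. Power is shown over a range of covariances: compound symmetry with ρ = 0.3, 0.5 and 0.7; random slopes with SD 0.3 and 0.5 per 18 months; AR(1) with 0.8 per 6 months.

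**1. The stated power.** A two-group comparison at one time point has noncentrality 0.65 × √(54/2) = 3.377. The two-sided normal approximation gives Φ(3.377 − 1.96) = 0.922. The t-test with 106 df gives 0.917, so β = 0.083, exactly as stated. The sample size therefore belongs to a single-time comparison, not to a test of slopes.

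**2. The slope.** With d(t) the between-arm difference, slope = Σ(t − 18)d(t) / Σ(t − 18)², and Σ(t − 18)² = 2 × (6² + 12² + 18²) = 1008.

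*(a) 0.65 at month 18, then maintained.* d = 0, 0.217, 0.433, 0.65, 0.65, 0.65, 0.65. The cross-product is 18.2 and the slope 18.2/1008 = 0.01806. Slope × 18 = 0.325 (true value 0.65); slope × 36 = 0.65 (true value 0.65).

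*(b) No difference to month 18, then rising to 0.65 at month 36.* The cross-product is again 18.2, so the slope is identical. Slope × 18 = 0.325 (true value 0); slope × 36 = 0.65 (true value 0.65).

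*(c) 0.65 at month 18, half lost by month 36.* The cross-product is 9.1. Slope × 18 = 0.1625 (true value 0.65); slope × 36 = 0.325 (true value 0.325).

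*(d) 0.65 at month 18, none left at month 36.* The cross-product is 0 and so is the slope.

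*(e) 0.65 at month 18, widening to 0.975 at month 36.* The cross-product is 27.3. Slope × 18 = 0.4875, which is 75% of 0.65.

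**3. Why these results line up.** When d(t) starts at 0 and bends only at month 18, it is the line d(36) × t/36 plus a triangle symmetric about month 18. The triangle contributes nothing to the slope. So slope × 36 = d(36) whatever happens at month 18, and slope × 18 = d(36)/2. In these patterns the slope is a test of the 36-month difference and carries no information on the 18-month one. If the bend comes earlier, that match is lost too. For a plateau already at month 6 the cross-product is 0.65 × 18 = 11.7, so slope × 36 = 0.418 against a true 0.65.

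**4. Power of the slope test across the assumed covariances.** (a) and (b): 0.75 to 0.999. (c): 0.26 to 0.78. (d): 0.05. (e): 0.98 to 1.00.

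**5. Piecewise model with a knot at month 18.** In (a), (c) and (d) it returns 0.65 at month 18 with power 0.90 to 0.999, and it also recovers the month-36 difference in each.

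**The case against.** The strongest reply is that the article does not say there is one straight line over 36 months. The word linear is set against logistic and Poisson regression and may only name the model family. A piecewise growth model also yields slopes to compare, and the time function is something an analysis plan, not shown here, would normally fix. This stands as a limit on confidence. It does not dispose of the point, because the article does choose the slope as its reported effect and links it to no month.

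A reader might also draw stronger conclusions, which the documents do not support:

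- *That the slope is wrong at both time points.* In (a) and (b), slope × 36 equals the true 36-month difference, the one the hypothesis stresses.
- *That power is halved.* Under the plateau the halving concerns slope × 18 only. The test keeps power of about 0.75 to 0.999, below the stated 92% mainly with large random slopes or AR(1) correlation.
- *That the fitted lines differ by only 0.325 at month 18.* With free intercepts the fitted difference there is the mean of the seven differences: 3.25/7 = 0.464 SD, or 71% of 0.65.
- *That the effect would be erased.* A zero slope needs full convergence by month 36, and the protocol expects the opposite. Under the widening in (e) the slope test is well powered.
- *That (a) and (b) can never be told apart.* If the model imposes a common baseline, slope × 18 is 0.34 to 0.42 in (a) and 0.23 to 0.31 in (b), and in (d) it is 0.03 to 0.19 rather than zero. These ranges also include independent residuals.

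Finally, if BPDSI is measured only at screening and month 36, the slope is simply the 36-month change divided by 36. The seven-visit arithmetic then does not apply, and the 18-month difference could not be estimated at all.

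**Conclusion.** The point holds as a moderate one. The reported contrast is not tied to the 18-month difference that justifies the sample size, nor explicitly to the 36-month difference that the hypothesis stresses. Read as one line over 0 to 36 months, it gives the 18-month effect only under linear divergence. In the patterns examined, slope × 18 ranges from three quarters of the true 18-month effect (continued widening), through half (maintained gain) and a quarter (half lost), to nothing (full convergence). Power suffers materially only when the arms converge after month 18.

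Every size given here rests on assumed trajectories and covariances, complete data, free arm intercepts, the straight-line reading and BPDSI at all seven visits. The protocol article fixes none of these, so the figures show what can happen and do not predict what will. A claim that the main analysis must fail is not supported.

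**What to change.** 1. Name the primary time point for the BPDSI, so that sample size, hypothesis and main contrast refer to the same month.
2. Use a piecewise-linear growth model with a knot at month 18, or a mixed model with visit as a categorical factor and arm-by-visit terms. Constrain baseline BPDSI to be equal across arms or use it as a covariate.
3. Report the adjusted arm difference with its interval at the primary time point, and at the other of 18 and 36 months as key secondary.
4. State clearly that the BPDSI is assessed at those visits.

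If the BPDSI is already collected every 6 months, this costs only wording in the analysis plan and uses the same data. The price is a few more parameters and a slightly wider interval if change really is linear.

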#### Health economic evaluation

We will estimate the difference in total costs for MBT-DH compared to TAU and the difference in clinically relevant effects of the treatments. By dividing the difference in costs by the difference in effectiveness, the incremental cost-effectiveness ratio (ICER) will be estimated. The ICER represents the extra amount of money that has to be invested or will be saved to gain or lose on extra unit of effect.

In the economic evaluation, all relevant costs and effects will be taken into account, meaning that we will use a so-called societal perspective, which is preferred in economic evaluations in The Netherlands [88]. The costs will include all costs made, that is, intervention costs, direct and indirect medical costs, as well as productivity losses and costs made elsewhere in the health care system. Using the societal perspective, clinically relevant effects are those effects that are meaningful for society. Moreover, in order to compare effects between allocations in health care, effects should be expressed in generic terms. We will therefore use QALYs and will express the cost-effectiveness and its ratio as cost per QALY. The use of QALYs is advised in guidelines for cost-effectiveness analysis, especially when main effects are expected in quality of life [89].

Our primary cost-effectiveness ratio will be estimated using empirical data only and therefore using a 3-year time horizon, which is equal to the trial duration. Cost data are generally highly skewed, and QALY scores and ICER values are not distributed normally in most cases. Therefore, the uncertainty intervals around the mean costs, mean effects and mean ICER values will be estimated using bootstrap simulations with 1000 replications [90-92]. These results will be graphically presented in cost-effectiveness planes. Various societal willingness-to-pay values will be used to estimate net monetary benefits. These net monetary benefits are then used to derive cost-effectiveness acceptability curves.

We will also explore the long-term costs and effects of MBT-DH and TAU from a societal perspective. One way of achieving this would be to use a Markov model to explore the long-term cost-effectiveness of the intervention under study. However, health stages in a Markov model are often predefined, discrete stages, where they should reflect the biological or theoretical understanding of the condition being modelled [93,94]. Because in this trial the BPDSI, which is a continuous measure, is the primary outcome measure, it does not allow for an unambiguous definition of health states to model disease progression. Having heterogeneous health states may be controversial, as it means that a wide range of patients may be clustered in one health state. In order to explore the cost-effectiveness using a Markov model in our study, we will therefore define health states on the basis of a cut-off score on one of the outcome measures such as the BPDSI or the OQ-45. We will extend the cost-effectiveness model results after the duration of the trial using different assumptions based on, for example, the literature. Sensitivity analysis will be performed in order to investigate the influence of those assumptions on the model results.

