### Research aims and hypotheses

The primary aim of the present study was to investigate the efficacy and cost-effectiveness of MBT-DH in comparison to a specialist TAU in The Netherlands. We expect both MBT-DH and specialist TAU to be effective on both primary and secondary outcomes. Yet, we expect MBT-DH to outperform TAU, particularly at 36 months follow-up. After 18 months of treatment we expect the costs in the MBT programme to be comparable to TAU; after 36 months we expect MBT-DH to outperform TAU (following Bateman & Fonagy [32]). Second, we will investigate purported mechanisms of change in MBT, focusing on changes in attachment and mentalizing. Results of this trial are expected to inform mental health professionals, patients, and policy makers.

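### The planned bootstrap interval around mean ICER values cannot be read if QALY differences come near zero, and is not ordered by value if MBT-DH is cheaper and better

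*Protocol article*

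**What the plan says.** All of the plan for this point stands in the protocol article, mainly under Health economic evaluation.

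- Definition: "By dividing the difference in costs by the difference in effectiveness, the incremental cost-effectiveness ratio (ICER) will be estimated". Effects are expressed as QALYs.
- Horizon of the primary ratio: the plan uses empirical data only, "therefore using a 3-year time horizon, which is equal to the trial duration".
- Uncertainty: "the uncertainty intervals around the mean costs, mean effects and mean ICER values will be estimated using bootstrap simulations with 1000 replications". The reason given is that costs are skewed and that QALYs and ICERs are usually not normally distributed.
- Display: "These results will be graphically presented in cost-effectiveness planes".
- Net benefit: "Various societal willingness-to-pay values will be used to estimate net monetary benefits", and "These net monetary benefits are then used to derive cost-effectiveness acceptability curves".

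Under Research aims and hypotheses, the cost expectations are "After 18 months of treatment we expect the costs in the MBT programme to be comparable to TAU" and, later, "after 36 months we expect MBT-DH to outperform TAU". The same section makes cost-effectiveness part of the primary aim.

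The article sets no rule for replicates with a QALY difference near or below zero, or for negative ratios. It gives no expected QALY difference and no variance for QALYs or costs.

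**The concern.** Bootstrapping deals with non-normality, which is the reason the article gives for using it. It does not cure two other properties of a ratio.

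1. **Sign.** A negative ICER arises when MBT-DH is cheaper and better, and also when it is dearer and worse. A positive ICER arises when it is dearer and better, and also when it is cheaper and worse. Percentiles taken over a mixture of these cases pool opposite conclusions.
2. **Order.** Among cheaper-and-better results, the size of the ratio does not rank them by value, because a larger QALY gain moves the ratio towards zero.

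There is a third problem if mean ICER is taken to be the average of the 1000 replicate ratios. When the denominator can come close to zero, a few replicates dominate that average.

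At stake is how the uncertainty of a headline economic result is reported. The Discussion criticises the earlier economic study for not using state-of-the-art methods and promises them here.

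**Working it through.** **The plan's own figure.** The article gives no number for the ICER interval. The nearest is the power for the BPDSI: 54 per arm, d = 0.65, α = .05 (two-sided assumed). Normal approximation: 0.65 × √(54/2) = 3.378; 3.378 − 1.960 = 1.418; Φ(1.418) = 92.2%. The noncentral t gives 91.7%, which matches the stated β of .083. The figure reproduces, but it concerns the BPDSI, not QALYs.

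**Sign.** A saving of 16,000 with a gain of .40 QALY gives −16,000/.40 = −40,000. An extra cost of 16,000 with a loss of .40 QALY gives 16,000/(−.40) = −40,000. The ratio is the same and the conclusion is opposite.

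**Order.** The earlier-trial costs quoted in the Background sum to 27,303 + 3,183 = 30,486 for MBT-DH and 30,976 + 15,490 = 46,466 for TAU, a saving of 15,980 dollars, or about 16,000. With that saving, a gain of .05 QALY gives −320,000 and a gain of .40 gives −40,000. The better result sits nearer zero. Net monetary benefit ranks them correctly: at an assumed 20,000 per QALY it is 20,000 × .05 + 16,000 = 17,000 against 20,000 × .40 + 16,000 = 24,000.

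**How often the QALY difference is negative.** With 54 per arm and a standardized QALY effect d, the expected share of replicates, centred on the true effect, is Φ(−d/√(2/54)), where √(2/54) = 0.192. The values of d are assumptions.

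| d | Share below zero |
|---|---|
| 0.2 | 14.9% |
| 0.3 | 5.9% |
| 0.4 | 1.9% |
| 0.65 | 0.04% |

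**Spread over quadrants.** Simulation of 400 trials × 1000 replicates per scenario. Assumptions not in the article: lognormal costs with coefficient of variation (CV) 0.5 to 1.5, and normal QALYs with SD 0.6, independent of costs. Costs are either the Background sums or equal in both arms (CV 1 only). Share of trials in which no quadrant held 95% of replicates:

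| d | Background costs, CV 0.5 to 1.5 | Equal costs, CV 1 |
|---|---|---|
| 0.2 | 73–88% | 97% |
| 0.4 | 32–67% | 94% |
| 0.65 | 4–51% | 91% |

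At d = 0.65 nearly all of this spread is between dearer and cheaper with a positive QALY difference. About 1% or fewer of replicates had a negative one.

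**Average of ratios.** In the same simulation (Background costs, CV 1), the average of replicate ratios divided by the ratio of mean differences had a 5th to 95th percentile range of −2.7 to 4.8 at d = 0.2, −2.3 to 3.9 at d = 0.4, and 0.4 to 1.6 at d = 0.65. The instability belongs to small QALY effects.

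**Coverage.** The percentile ICER interval covered the true ratio in 93–99.5% of simulated trials. The net-benefit interval at 20,000 per QALY covered in about 91–96%. The ICER interval therefore shows no loss of coverage. The gain from net benefit is that its limits can be read.

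**The case against.** The strongest reply is that the same section already supplies most of the remedy. It plans intervals for costs and effects, planes that show the quadrant spread, net monetary benefits and acceptability curves. It also defines the ICER as a ratio of differences, so mean ICER values may be loose wording rather than an average of replicate ratios. All of this stands. It confines the point to the ICER interval and to the net-benefit interval, which is not stated.

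A reader might infer three stronger things, none of which the article supports.

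- **That the trial's own expectations make a spread over several quadrants likely.** Comparable costs are expected at 18 months, but the primary ratio is at three years, where the expectation points to cheaper and better. The Background says differences may be smaller in The Netherlands, but gives no QALY figure. An assumed gain of .05 QALY (SE .10) and saving of 2,000 (SE 8,000) puts Φ(−.05/.10) = 31% of replicates below zero. Those inputs imply an SD of .10/0.192 = .52 and d of about 0.10. With the same SEs, a saving of about 16,000 and d = 0.4, about 96% of replicates are cheaper and better.
- **That the interval is invalid or is not a confidence interval.** The coverage results do not show this. Where all QALY differences are positive, a ratio below a willingness-to-pay value still means positive net benefit at that value, so part of the reading survives.
- **That the economic conclusion rests on this interval.** It does not, given the other planned outputs.

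Quadrant handling is also a detail that a condensed article may leave to a fuller plan. But the interval itself is a stated method, not an omission, and it is hard to read even if the 36-month expectation is met.

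**Conclusion.** The point holds in a limited form. An interval around the ICER cannot be interpreted if replicates have QALY differences near or below zero. This is plausible with 54 per arm and a small QALY difference, but its extent rests on an assumed effect and variance. Independently of that, the limits are not ordered by value in the cheaper-and-better case that the article expects at 36 months. The instability of a mean of ratios applies only if mean ICER is meant that way and the QALY effect is small. The fault lies in interpretation and reporting. It does not touch coverage, sample size, power or the clinical analyses. It is worth correcting because cost-effectiveness is part of the primary aim and the change is small.

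**What to change.** - Report the ICER only as the ratio of the mean cost difference to the mean QALY difference.
- Attach no bootstrap interval to it unless the replicates lie where the ratio is ordered, that is, with positive QALY and positive cost differences.
- Express uncertainty through the cost and QALY intervals, the plane and the acceptability curve already planned.
- Add the proportion of replicates in each quadrant, and bootstrap intervals for incremental net monetary benefit at stated willingness-to-pay values.

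This takes a sentence or two in the analysis text and uses the same 1000 replicates, with no new data. The small downside is that in most cases the ICER itself will carry no interval, which some readers of economic evaluations will look for.
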